#### Sociodemographic measures

Participant characteristics (eg, date of birth, gender, ethnicity, marital status, education, employment status and income) will be collected at baseline. Residential postcode will be recorded at baseline, with participants asked at 12 week and 12 month follow-up whether they have moved residence, with those who have asked to provide their new postcode.

### Economic evaluation

The economic evaluation will explore the cost-effectiveness, cost-utility and cost-consequences of the Cycle Nation intervention compared with the existing national standard single group-based cycle training session over 12 months and following a prespecified Health Economics Analysis Plan. The resources required to deliver the Cycle Nation intervention and the standard session will be identified, measured and valued, and include:

Facilitator training costs.Participants’ cycle training.Training programme delivery costs.Any facilities costs incurred.Materials provided for intervention costs.Capital items (eg, cost of bikes/bike loan; helmets and locks).Reusable.

Resource use data will be combined with unit costs from national databases and routine sources relative to a reference year. Within-trial healthcare, social care and personal resource use data will be measured through the outcome questionnaire to identify frequency and costs related to:

General practitioner visits.Nurse visits.Hospitalisations (including Attendances and Emergency and out-patient).Over the counter medications and lifestyle products (eg, slimming aids).Costs of gym membership and/or classes.Costs of previously purchased fitness/health apps.Average time spent exercising and walking daily.Cycling frequency and distance.Employment.Total annual household income.

For the economic outcomes, Quality Adjusted Life Years (QALYs) will be derived using the EQ-5D-5L (21) instrument combined with within-trial duration (months) and the Years in Full Capability (YFC) will be derived using the ICECAP_A instrument (25) combined with within-trial duration (months).

A National Health Service and personal social service perspective will be used for the base case economic evaluation. Sensitivity analyses using a broader societal perspective will also be conducted.

### Process evaluation

A mixed-methods process evaluation, embedded within the RCT and guided by the MRC Process Evaluation Framework,^30^ will examine the reach, delivery, mechanisms of impact and contextual influences of the Cycle Nation intervention. The evaluation will explore potential unintended consequences and variation in delivery across participating community cycling organisations.

Participant interviews: In-depth semistructured interviews will be conducted with approximately 25 participants, with one to two participants from each Cycle Nation group (45–60 minutes, by telephone or using online software). The same participants will be interviewed at both 12 week and 12 month follow-up to explore mechanisms of change and factors influencing sustained cycling. In addition, all non-completers (defined as attending fewer than six sessions or reporting discontinuation) will be invited to a shorter interview (approximately 30 minutes) to explore reasons for non-completion and barriers to engagement.

Questionnaires: A brief post-intervention participant questionnaire will assess the acceptability of programme content, perceptions of facilitators and delivery venue, and cycling equipment. At the 12 month follow-up, additional questions will explore sustained use of programme strategies and ongoing contact with peers and facilitators. These questions will be embedded within the outcome questionnaires for intervention participants.

Facilitator perspectives: Cycle Nation facilitators will participate in interviews or focus groups (45–60 minutes, in person, by telephone or online) after they have finished delivering all their allocated Cycle Nation groups to capture experiences of programme delivery, supporting participant engagement and perceived barriers and facilitators to implementation. Facilitators will complete a structured proforma immediately after each session to record fidelity of delivery, time spent on preparation and a description of how and why any key delivery points were not delivered as intended.

Observations: Two sessions per group will be observed by trained fieldworkers, including session four for most groups and one additional session sampled across groups. Observations will include items on fidelity of session delivery and field notes to provide a thick description of fidelity, delivery style and participant engagement.

#### Uptake, adherence and retention

The research team will record the number of individuals who express interest, are eligible, consent and are randomised to an intervention. Reasons for withdrawal will be recorded, if provided.

The cycle facilitators will submit weekly attendance registers via Microsoft Teams. Reasons for missed sessions will be collected, and attendance at six sessions, including ‘catch-ups’ when required, will define completion. Comparator group attendance at the single session will also be recorded.

### Sample size calculation

The primary outcome is the proportion of participants reporting cycling for any purpose at least weekly at 12 months. The study has been powered to detect a difference of 2 in 10 people cycling at least weekly between groups (ie, 10% vs 30%, 20% vs 40%, 30% vs 50%, 40% vs 60%, etc). A sample size of 214 participants (107 per group) provides 80% power to detect a 20% absolute difference in cycling prevalence (40% vs 60%) and a 0.38 SD difference in continuous outcomes at a 5% significance level. To account for an anticipated 20% loss to follow-up, the sample size will be inflated by 25%, yielding a maximum of 268 participants (134 per group). Participants enrolling together will be treated as a single randomisation unit; few such clusters are expected, and their impact on statistical power is minimal.

### Randomisation

#### Sequence generation, allocation concealment mechanism and implementation

Randomisation to the intervention and comparator group will be predominantly simple individual (1:1). However, during screening, participants will be asked if they know anyone else (eg, friends, family) who is planning to join the study. If the other person is eligible and enrolled within 7 days, they will be randomised together to reduce contamination. This small-scale clustering is factored into sample size and analysis. The randomisation sequence will be computer generated and implemented via a telephone interactive voice response system. Participant enrolment and randomisation to intervention or comparator will be undertaken by members of the research team and fieldworkers.

#### Blinding

Participants cannot be blinded to their allocation due to the nature of the intervention. Researchers undertaking the statistical analyses will be blinded to group allocation. There will be no circumstances in which the participants’ allocation will be revealed to the analysis team prior to analysis. Other study team members will not be blinded as they will be involved in allocating participants to intervention deliveries and conducting session observations and interviews.

### Data management

A member of the research team will review the data after a participant has completed a questionnaire and will contact participants if there are any unusual entries (eg, unexpectedly high/low values) to ensure data quality. Data will be exported from Qualtrics and saved securely on a University of Glasgow study server. A study-specific data management plan has been developed and submitted to the University of Glasgow Data Protection team.

### Statistical analysis

#### Outcome evaluation

A full statistical analysis plan (SAP) will be finalised prior to any unblinded analyses. The Roberston Centre for Biostatistics (Glasgow Clinical Trials Unit), University of Glasgow, will provide statistical services in support of delivering the trial.

The primary outcome will be compared between groups using a mixed effects logistic regression model, allowing for clustering and adjusting for important baseline characteristics, and reported as an adjusted OR, with 95% CI and p value. Absolute differences will also be reported. Analyses will follow intention-to-treat principles. Appropriate regression-based methods will be applied to secondary outcome measures. Missing data will be managed using multiple imputation with chained equations, applied separately within groups. Complier average causal effects methods will be applied to estimate the effects of the intervention for those who engage, as well as the effects of increased cycling on other outcomes. Sensitivity analyses will determine the association between attendance at intervention sessions and effectiveness. Subgroup analyses will be pre-defined in the SAP.

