### Intervention: Cycle Nation

#### Content and structure

Cycle Nation is a multi-component individual- and social-level cycling intervention consisting of nine, weekly interactive sessions, each lasting approximately 90 minutes, delivered to groups of up to 10 participants. Sessions will be led by two trained cycle facilitators covering off-road and then on-road cycle skills training as well as cycle maintenance training (eg, fixing a dropped chain), information-sharing activities and behaviour change techniques (eg, weekly goal setting). Two optional 90 minute ‘catch-up’ sessions will be offered to any group in which more than two participants have missed three or more sessions by the end of session 7. These sessions are designed to help participants feel safe and confident on the roads. Detailed content is available in table 2.

**Table 2 T2:** Content of Cycle Nation programme

Session (week)	Discussion and behaviour change techniques	Practical	Practice ‘in own time’
0: Collect bicycle and equipment	N/A	N/A	N/A
1: On your bike	Overview of Cycle Nation Training Why Cycle?	Helmet, lights and lock ABC check Adjusting seat height Starting and stopping effectively	Lock your bike ABC check Ride your bike
2: Going through the gears	Review of ‘in your own time’ tasks What to wear Introduction to personal cycling goals	ABC check Going through the gears	ABC check Ride your bike Try out changing your gears
3: Basic cycling skills	Review of ‘in your own time’ tasks A brief introduction to barriers Buying a bike Personal cycling goals	Fixing a dropped chain Bike handling—cornering	ABC check Ride your bike Fix a dropped chain
4: Consolidating cycling skills	Review of ‘in your own time’ tasks Personal cycling goals	Pumping tyres Avoiding obstacles Front wheel lift Group (off-road) riding	ABC check Ride your bike Pump tyres Front wheel lift
5: Using the road	Review of ‘in your own time’ tasks Involving others Your rights on the road Personal cycling goals	Signalling Emergency stop Introduction to on-road riding	ABC check Ride your bike Practice signalling and emergency stops
6: On the road again	Review of ‘in your own time’ tasks Overcoming barriers Personal cycling goals	Lubricating the chain Traffic lights and roundabouts Filtering through queued traffic	ABC check Ride your bike Practise traffic lights
7: Puncture clinic	Review of ‘in your own time’ tasks Personal cycling goals	Replacing an inner tube	ABC check Ride your bike Change your inner tube

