8: Planning a journey	Review of ‘in your own time’ tasks Overcoming setbacks Route planning Long term bike access Personal cycling goals	Riding a planned journey	ABC check Ride your bike Plan a group ride
9: Moving forwards	Review of ‘in your own time’ tasks Action planning and moving forwards Graduation	Group ride	Keep riding
10 & 11: ‘Catch up’ (optional)	Welcome back and review Your rights on the road Personal cycling goals	Signalling Road positioning Traffic lights Filtering through traffic Roundabouts	Keep riding

ABC, air, brakes, chain; N/A, not applicable.

Rides between sessions: cycle facilitators will organise two additional led rides (approximately 90 minutes) between the sessions from weeks 5 to 9 once participants have progressed to on-road cycling. Participants will be encouraged to cycle between sessions to embed cycling into daily life, including meeting up with other group members to practise skills and build confidence.

WhatsApp: participants will be invited to join a WhatsApp group with the facilitators and group members. This will help to build peer support, with the facilitators sharing motivational messages to encourage cycling between, and attendance at, sessions.

Bicycle provision and equipment: participants will be loaned a bicycle, helmet, lock and lights for the duration of the intervention to reduce financial barriers and support engagement, especially for those uncertain about taking up cycling. Participants will receive a handbook covering course content.

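### The planned CACE for the effect of increased cycling on other outcomes needs an exclusion restriction that the programme's own content makes implausible for psychosocial and well-being outcomes

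*Protocol article*

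**What the plan says.** Outcome evaluation (under Statistical analysis) names two CACE targets in one sentence. The first is programme receipt: "Complier average causal effects methods will be applied to estimate the effects of the intervention for those who engage". The second takes cycling itself as the exposure: "as well as the effects of increased cycling on other outcomes". The other outcomes, the definition of increased cycling and the instrument are not named, and a full SAP is to follow.

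The Secondary objectives and Secondary outcomes sections list the candidates:
- psychosocial and well-being measures: motivation, confidence, perceived safety, self-esteem, vitality, capability well-being and health-related quality of life
- perceptions of the environment and physical activity
- journeys by private car, taxi and public transport, and on foot.

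The intervention's Content and structure section describes weekly goal setting and other behaviour-change techniques, delivered in groups. Of the WhatsApp group it says: "This will help to build peer support, with the facilitators sharing motivational messages". The Strengths and limitations box states that every outcome is self-reported, and Blinding states that participants know their allocation.

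**The concern.** Only allocation is randomised, so a CACE for cycling must use arm as the instrument. It divides the between-arm difference in the outcome by the between-arm difference in cycling. The ratio is the effect of cycling only if arm reaches the outcome through cycling and by no other route (the exclusion restriction). With one binary instrument and one exposure, the trial data cannot test this.

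The programme works on several secondary outcomes by other routes. Coaching can raise motivation, group membership can raise well-being, and skills training can raise confidence, whether or not the person cycles more at follow-up. The Introduction itself lists confidence and peer support among the factors that shape participation, so for confidence the direction from cycling to outcome is also in doubt.

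If the estimand is applied to these outcomes as written, effects of coaching and group contact would be credited to cycling.

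**Working it through.** **1. The plan's own figures.** Sample size calculation gives 107 per group for 40% vs 60% at 80% power and 5% significance (taken as two-sided).
- Without continuity correction: n = (1.96 × √(2 × 0.5 × 0.5) + 0.842 × √(0.24 + 0.24))² / 0.20² ≈ 97 per group.
- With continuity correction: 107 per group, 214 in total, as stated.
- Allowing for 20% loss: 214 / 0.80 = 267.5, rounded to 268, as stated.
- The same section claims "a 0.38 SD difference in continuous outcomes at a 5% significance level"; 107 per group gives 79.4% power for 0.38 SD, in line with 80%.

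The design difference in weekly cycling of 0.60 − 0.40 = 0.20 is therefore a fair value for the denominator of the ratio.

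**2. What differs between the arms apart from cycling.**

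| | Cycle Nation | Comparator |
|---|---|---|
| Scheduled contact | 9 sessions × about 90 min = 810 min (13.5 h) | 1 session of about 2 h |
| Group size | up to 10 | up to 6 |
| Goal setting, behaviour-change techniques | yes | none described |
| WhatsApp peer group | yes | none described |
| Skills and confidence training | yes | yes |

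Only the last row is shared. Reporting by unblinded participants is a further route from arm to outcome.

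**3. The bias.** Let β be the true effect of weekly cycling on an outcome in SD units, d the net between-arm direct effect in SD units, and Δ the difference in cycling.
- Between-arm difference in the outcome = βΔ + d
- CACE estimate = (βΔ + d) / Δ = β + d/Δ
- With Δ = 0.20, bias = d / 0.20 = 5d
- With Δ = 0.10, bias = 10d; with Δ = 0.40, bias = 2.5d

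**4. Size over assumed values.** The protocol gives neither β nor d, so both are assumptions here (Δ = 0.20). Each cell shows the estimate in SD units, with its ratio to the truth in parentheses.

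| d (SD) | β = 0.1 | β = 0.3 | β = 1.0 |
|---|---|---|---|
| −0.05 | −0.15 (sign reversed) | 0.05 (0.17) | 0.75 (0.75) |
| 0 | 0.10 (1.0) | 0.30 (1.0) | 1.00 (1.0) |
| 0.02 | 0.20 (2.0) | 0.40 (1.3) | 1.10 (1.1) |
| 0.05 | 0.35 (3.5) | 0.55 (1.8) | 1.25 (1.25) |
| 0.10 | 0.60 (6.0) | 0.80 (2.7) | 1.50 (1.5) |
| 0.20 | 1.10 (11) | 1.30 (4.3) | 2.00 (2.0) |

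A simulation of 2,000,000 records with β = 0.3 and cycling confounded with the outcome gave 0.31, 0.80, 1.31 and 0.05 for d = 0, 0.10, 0.20 and −0.05. The formula gives 0.30, 0.80, 1.30 and 0.05.

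**5. The same result as a share.** If a fraction s of the between-arm difference in the outcome is direct, the ratio to the truth is 1/(1 − s). A threefold overstatement needs s of at least two thirds.

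**The case against.** The strongest reply is that the protocol does not say which outcomes will be analysed this way. Car, taxi and public transport journeys are natural targets, and for them a route that bypasses cycling is less evident. This stands, and it is why removing the whole estimand would go too far.

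Only the net difference between arms causes bias, and the comparator also trains skills and confidence in a group. This stands as well and makes d smaller than the programme description alone suggests. It does not make d zero, because contact time, goal setting and peer support remain one-sided.

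Two pieces of text need care. The motivational messages are meant to encourage cycling and attendance, so they act partly along the permitted path; peer support is the clearer direct route. The sentence "These sessions are designed to help participants feel safe and confident on the roads" directly follows the description of the optional catch-up sessions and may refer only to them. The argument does not depend on it.

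A reader might infer three stronger points that the document does not support:
- **The estimate is inflated fivefold, or several-fold.** Five multiplies the unknown d; it is not the ratio of estimate to truth. The ratio and the sign depend on values the protocol does not give.
- **The CACE for those who engage is also invalid.** The Uptake, adherence and retention section defines completion as six sessions, but nothing equates that with engagement. The exposure definition properly belongs to the SAP.
- **The attendance analysis makes an unsupported causal claim.** The text is "Sensitivity analyses will determine the association between attendance at intervention sessions and effectiveness", which claims an association only.

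Finally, it can be said that the SAP will settle the matter. It can do so by narrowing or qualifying the estimand. Further modelling detail alone would not make the assumption hold for outcomes that the programme addresses directly.

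**Conclusion.** The point holds for the psychosocial and well-being outcomes: motivation, confidence, perceived safety, self-esteem, vitality and well-being. For these, the protocol's description of the two arms makes the exclusion restriction implausible, and a CACE for increased cycling would mix programme effects with cycling effects. For motorised transport the assumption is more tenable, although unblinded self-report still applies.

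The bias is 5d at the design difference of 0.20. The overstatement could be none, modest or several-fold, and a negative d biases downward. These figures assume that arm is the instrument, that the exposure is weekly cycling yes/no, and that the achieved difference equals the design value. Another exposure scale or another achieved difference changes the multiplier but not the argument.

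The analysis is supplementary. The primary intention-to-treat comparison and the CACE for programme receipt are not called into question.

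**What to change.** Amend the sentence in Outcome evaluation and carry the change into the SAP:

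- Name the outcomes for which the effect of increased cycling will be estimated by CACE, and limit them to those where the exclusion restriction can be argued, for example car, taxi and public transport journeys. Give the argument for each.
- For psychosocial and well-being outcomes, either drop the causal claim or label the analysis exploratory.
- If it is kept as exploratory, report it over a prespecified range of net direct effects: adjusted estimate = CACE estimate − (d ÷ difference in cycling). For example, an estimate of 0.80 SD with d = 0.10 and a difference of 0.20 becomes 0.80 − 0.50 = 0.30 SD. The range should include negative d.
- Alternatively, use exploratory mediation analysis with its assumptions stated. This exchanges the exclusion restriction for the assumption of no unmeasured mediator–outcome confounding, which is also untestable, so it should not be presented as a stronger causal claim.

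The cost is a change of wording and a small additional analysis. The trial gives up or qualifies one causal claim; data collection, sample size and the primary analysis do not change.

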#### Economic evaluation

Within-trial results for the cost-utility and cost-effectiveness analyses will be presented as mean cost, mean effect and incremental cost-effectiveness ratios (ICER), that is, the incremental cost-per-unit of increase in the proportion of participants cycling at least weekly. For all economic analyses, the mean cost and mean outcome (increase in cycling, QALYs and YFC) associated with the intervention and comparator groups will be estimated using a generalised linear model, which will tackle the non-normality of data, adjusting for relevant covariates (eg, demographics). Non-parametric bootstrapping techniques will explore uncertainty around estimated costs, outcomes and the ICER. Costs, combined with QALYs, will be presented on the incremental cost-effectiveness plane.^31^ Joint uncertainty in costs and outcomes will be represented on a cost-effectiveness acceptability curve and the prevailing UK willingness-to-pay thresholds for cost-effectiveness will be employed.^32^ A multiple imputation procedure using chained equations will be used to impute missing outcomes and resource use separately for each arm of the trial, and predictive mean matching will allow dealing with the non-normality of cost and outcome data.^33^ The economic evaluation will be reported and presented in line with current economic evaluation methods guidance.^34^ An incremental cost-consequences analysis will document all intervention costs and consequences compared with the control. Several sensitivity analyses will be run to explore the sensitivity of results to changes in parameters including intervention costs.

#### Process evaluation

Recruitment, attendance, completion data and participant baseline characteristics will be summarised using descriptive statistics (means, SD and proportions). Descriptive statistics will be used to summarise participant characteristics, responses from the attendance sheets, acceptability questionnaires and facilitator delivery proformas. Data will be input in Excel and analysed using analytic software, for example, SPSS. Descriptive summaries will present session attendance, number of sessions delivered and fidelity to key programme components, allowing identification of variation and patterns of incomplete delivery. Differences in baseline characteristics between those who participated, those who did not and those who discontinued will also be examined to identify patterns of engagement.

Qualitative data from participant interviews (including non-completers), facilitator interviews and focus groups will be audio recorded, transcribed verbatim, deidentified and uploaded into NVivo software for analysis. Field notes from observations will be incorporated to provide additional insights into fidelity and participant engagement. A thematic framework approach^35^ will be used to explore participant experiences, mechanisms of change and contextual factors influencing delivery and sustained cycling.

Following separate quantitative and qualitative analyses, findings will be compared and integrated across data sources. This triangulation will allow examination of how context, implementation and mechanisms of action influenced trial outcomes and will help identify barriers and facilitators to delivery, engagement and long-term behaviour change.

